### Basic body awareness therapy – a physiotherapeutic mind-body therapy

#### Studies I and II

This comprises ten weekly sessions for a group of five to seven participants with one instructor responsible for all sessions. Three physiotherapists, with special BBAT education and clinical experience of being BBAT instructors are recruited for both group and individual sessions in both studies. Before intervention, the BBAT instructors meet and synchronize how they will perform the interventions. The patients are clustered by BBAT instructors. Patients will also be clustered by the set of five to seven participants included in each group. We will test associations between depression symptoms, instructors and group. Only one room will be used for all group sessions in each study. Breathing, grounding, stability in the central line, centring, flexibility and flow are features systematically trained at each session. Patients are encouraged to observe and accept the sensations and emotions that awaken during the treatment situations. Patients systematically train to discern and differentiate between thoughts, emotions and body sensations. Continuous training and repetition are fundamental parts of BBAT [36].

Patients are offered five individual sessions where they focus on their own particular difficulties.

To balance the two intervention methods patients participating in fewer than five group sessions will not be offered any individual sessions. The total participation rate will be counted.

Enhanced body awareness and a greater unity between body and self are important goals [33]. Body awareness is the subjective, phenomenological aspect of proprioception and interoception that enters conscious awareness, and is modifiable by mental processes including attention, interpretation, appraisal, beliefs, memories, conditioning, attitudes and affects [33]. Important in BBAT is breathing, which is regarded as a central connector between body and mind. Improved body and mind integration is achieved by noticing, discerning, and differentiating thoughts, emotions and body sensations [33].

### Measures to enhance participation

In both studies, participants are offered ‘preventive sick leave’ for the time spent in group or individual sessions by the Swedish Social Insurance Agency, as a measure to enhance participation.

### Discontinuation of intervention with ASSA and BBAT

In both studies, if anything should happen to patients during the intervention so that they fulfil the exclusion criteria, they will be advised to withdraw. In case of psychiatric complications as a result of the interventions, patients will be offered personal counselling or referral to a psychiatric unit.

### Treatment as usual

In both studies, there will be no restriction on the use of treatment as usual, such as psychotherapeutic or physiotherapeutic treatment, antidepressant medication or diabetes-related treatment.

### Primary and secondary outcome measures

In both studies, the primary outcome measure is the change in depression symptoms. Secondary outcome measures are changes in alexithymia and anxiety symptoms and self-image measures; changes in HbA1c concentration and midnight salivary cortisol concentration; use of antidepressants, and incidence of diabetes complications and mortality.

### Power calculations for sample size

The standard deviation was 2.8 for the individual changes of Hospital Anxiety and Depression Scale – depression subscale after our intervention with ASSA for patients with chronic benign pain (calculated from raw data) [32].

#### Study I

If we assume that the standard deviation for the individual changes in Hospital Anxiety and Depression Scale – depression subscale in this study is 2.8, a change of 1.4 points represents half the standard deviation, which is considered indicative of clinically relevant changes in subjective symptoms [52]. Calculating a statistical power of 80 %, and assuming significance at the 0.05 level, 64 persons in each intervention arm are required at follow-up in a two-arm randomized controlled trial. Unfortunately we only recruited around 21 persons in each arm in Study I, rendering a power of 37 %.

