**Methods:**

Two studies will be performed. Study I is an open-labeled parallel-group study with a two-arm randomized controlled trial design. Patients are randomized to either affect school with script analysis or to basic body awareness treatment. According to power calculations, 64 persons are required in each intervention arm at the last follow-up session. Patients with type 1 or type 2 diabetes were recruited from one hospital diabetes outpatient clinic in 2009. The trial will be completed in 2016. Study II is a multicentre open-labeled parallel-group three-arm randomized controlled trial. Patients will be randomized to affect school with script analysis, to basic body awareness treatment, or to treatment as usual. Power calculations show that 70 persons are required in each arm at the last follow-up session. Patients with type 2 diabetes will be recruited from primary care. This study will start in 2016 and finish in 2023. For both studies, the inclusion criteria are: HbA1c concentration ≥62.5 mmol/mol; depression, alexithymia, anxiety or a negative self-image; age 18–59 years; and diabetes duration ≥1 year. The exclusion criteria are pregnancy, severe comorbidities, cognitive deficiencies or inadequate Swedish. Depression, anxiety, alexithymia and self-image are assessed using self-report instruments. HbA1c concentration, midnight salivary cortisol concentration, blood pressure, serum lipid concentrations and anthropometrics are measured. Data are collected from computerized medical records and the Swedish national diabetes and causes of death registers.

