#### Study II

The power calculation is based on an analysis of variance (ANOVA), where two groups have the same means and one differs with 1.4 points, using the same standard deviation (2.8) as in Study I. Calculating a statistical power of 80 %, calculated using an ANOVA, 60 persons are required. However, using the Kruskal–Wallis test reveals that it is necessary to increase this by 15 %; thus, 70 persons are required in each arm in a three-arm randomized controlled trial.

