### Statistical analysis

#### Study I

The Wilcoxon signed rank test and the Kruskal–Wallis test will be used for changes in non-normally distributed variables (for psychological symptoms measured using the self-report instruments and for midnight salivary cortisol concentration).

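### Study I's 64 per arm and 37% power fit a parametric comparison and omit the 15% increase that the protocol applies to Study II for the Kruskal–Wallis test

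*Protocol article*

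**What the plan says.** The primary outcome in both studies is change in depression symptoms, scored on the depression subscale of the Hospital Anxiety and Depression Scale (HADS-D). The sample size section takes its spread from an earlier trial of the same intervention: "The standard deviation was 2.8 for the individual changes of Hospital Anxiety and Depression Scale" (depression subscale).

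For Study I, "a change of 1.4 points represents half the standard deviation". The targets are 80% power and a 5% significance level, and the section concludes that "64 persons in each intervention arm are required at follow-up in a two-arm randomized controlled trial". No test is named. The section then reports the shortfall: "we only recruited around 21 persons in each arm in Study I, rendering a power of 37" per cent.

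For Study II, with the same SD and the same difference, an ANOVA calculation gives 60 per arm. The section adds that "using the Kruskal–Wallis test reveals that it is necessary to increase this by 15" per cent, which leads to 70 per arm.

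The Study I part of the statistical analysis section states: "The Wilcoxon signed rank test and the Kruskal–Wallis test will be used for changes in non-normally distributed variables", and lists psychological symptoms from the self-report instruments among those variables. The Study II part names the Kruskal–Wallis test for the same variables. A separate paragraph covering both studies assumes about 10% non-response and raises inclusion accordingly.

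**The concern.** The two studies share the primary outcome, the SD, the target difference and the planned between-arm test. The Wilcoxon signed rank test also listed for Study I is a paired test, so the Kruskal–Wallis test is the one that compares the arms. Only Study II was sized for it. If the 15% is needed there, it is needed in Study I as well; without it, the stated size and power belong to a test that is not the one planned for this outcome.

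What is at stake is the stated precision of Study I. The protocol says that the results of the two studies will be compared, so their power statements should rest on one basis. On the protocol's own rule, 64 per arm would not deliver 80% power, and 21 per arm would not deliver 37%.

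**Working it through.** **Inputs from the protocol.** Difference 1.4 points; SD of change 2.8; standardised difference d = 1.4/2.8 = 0.5; significance level 0.05; target power 80%; about 21 per arm achieved; rank-test increase 15% (stated under Study II); non-response 10%. Sidedness is not stated. Two-sided is used here because it reproduces 64; a one-sided test would need 50 per arm.

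**Step 1: reproduce the stated figures.**
- Size, normal approximation: n = 2 × (1.96 + 0.84)² / 0.5² = 62.8, so 63. With the noncentral t distribution: 63.8, so **64**, as stated.
- Power at 21 per arm, normal approximation: Φ(0.5 × √(21/2) − 1.96) = Φ(1.620 − 1.960) = **36.7%**, which rounds to the stated 37%. The t test gives 35.3% at 21 per arm and 36.7% at 22.

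Both figures therefore belong to a parametric two-sample comparison with no rank-test allowance.

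**Step 2: Study II's rule.** 60 × 1.15 = 69, stated as 70. The 15% corresponds to an efficiency of 1/1.15 = 0.870, close to the worst-case value of 0.864 for a rank test against the t test. For normal data the efficiency is 3/π = 0.955.

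**Step 3: apply the same rule to Study I.** Required size: 64 × 1.15 = 73.6, so **74 per arm**. With normal data: 64 × π/3 = 67.0, so about **67 per arm**.

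For power, use effective n = n/1.15 or n × 0.955:

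| Per arm | Basis | Effective n | Power (t) | Power (normal approx.) |
|---|---|---|---|---|
| 64 | 15% rule | 55.7 | 74% | 75% |
| 64 | efficiency 0.955 | 61.1 | 78% | 79% |
| 21 | no allowance | 21 | 35.3% | 36.7% |
| 21 | efficiency 0.955 | 20.1 | 33.9% | 35.3% |
| 21 | 15% rule | 18.3 | 31.2% | 32.7% |

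A simulation of the two-group rank test on normal data (40,000 runs) gives 33.4% at 21 per arm, 78.1% at 64 and 80.2% at 67.

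**Step 4: detectable difference at 21 per arm, 80% power (t).** No allowance: 0.886 × 2.8 = 2.48 points. Efficiency 0.955: 0.908 × 2.8 = 2.54. 15% rule: 0.954 × 2.8 = 2.67. The range is **2.5–2.7 points**, against a target of 1.4.

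**Step 5: conditional on 21 being a count before loss.** 21 × 0.9 = 18.9, so about 19 analysed. Power at 19 per arm is 28.6% (t) to 30.1% (normal approximation) under the 15% rule, 31.0% (t) to 32.5% (normal approximation) with efficiency 0.955, and 32.3% (t) with no allowance: about **29–32%**.

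**The case against.** The strongest reply is that nothing has been miscalculated. A reader might infer that 64 and 37% are arithmetic errors, or that 37% should read 35%. The document does not support that. Both figures follow from the stated inputs, the Study I section never claims that they apply to a rank test, and the arm size is given only as approximately 21. One more person per arm brings the t-test power to 36.7%. This part of the reply stands in full.

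Second, 15% is a conservative allowance. With normally distributed changes the rank test costs about 5%, so 74 per arm is not an absolute requirement. This stands too, and is why 67 per arm and 34% are given alongside. It does not remove the inconsistency: the authors themselves call the 15% necessary, and their analysis section classes these variables as non-normal.

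Third, a reader might infer that power has certainly fallen further through non-response. The 10% is an allowance for how many to include. Although the text says recruited, it does not settle whether the 21 is before or after loss, so the 29–32% is conditional.

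Fourth, a reader might infer that the abstract misleads, because it says that "64 persons are required in each intervention arm at the last follow-up session" and omits the 21. But that sentence states a requirement, consistent with the body, and does not claim that 64 were recruited. The power section gives the shortfall, and the Discussion lists insufficient participation as a limitation. What the abstract includes is a reporting preference, as is any wording about confidence intervals or non-significant results.

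Finally, recruitment took place in 2009, so no restated size can change Study I. That is true, and it limits the point to a correction of stated figures.

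**Conclusion.** The point holds as a consistency correction. Study I's size and power were stated for a parametric comparison, while its planned between-arm test for the primary outcome is one for which the same document requires 15% more participants. On that rule the requirement rises by 10 per arm (64 to 74), 64 per arm gives about 74% power rather than 80%, and 21 per arm gives about 31–33% rather than 37%. If the changes were normally distributed, the shift is smaller: about 67 per arm, and about 34% power at 21 per arm.

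These results assume a two-sided 0.05 level, equal arms, SD 2.8, and exactly 21 per arm where the protocol gives an approximate number. The gap of roughly 3 to 6 points in power does not change the conclusion that the authors already draw: Study I is badly underpowered for 1.4 points.

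**What to change.** In the Study I power section, name the test to which the figures apply and restate them on the Study II basis:

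- about 74 per arm required at follow-up under the 15% rule (about 67 if the changes were normally distributed);
- about 31–33% power for 1.4 points at about 21 per arm (about 34% with efficiency 0.955);
- a difference of about 2.5–2.7 points detectable with 80% power at that size.

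State whether the 21 is the number recruited or the number analysed. If it is before the assumed 10% non-response, give the power as about 29–32%. Where the abstract repeats the 64, bring it into line.

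The cost is a few sentences of text. The design, the data collection and the planned test are untouched; the stated power becomes slightly less favourable.

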#### Study II

The power calculation is based on an analysis of variance (ANOVA), where two groups have the same means and one differs with 1.4 points, using the same standard deviation (2.8) as in Study I. Calculating a statistical power of 80 %, calculated using an ANOVA, 60 persons are required. However, using the Kruskal–Wallis test reveals that it is necessary to increase this by 15 %; thus, 70 persons are required in each arm in a three-arm randomized controlled trial.

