#### Study II

The main aim is to compare ASSA, BBAT with only treatment as usual in patients with type 2 diabetes, psychological symptoms and inadequate glycemic control.

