#### Study II

The Kruskal–Wallis test will be used for changes in non-normally distributed variables (psychological symptoms and midnight salivary cortisol concentration).

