## Discussion

Diabetes is a progressive and demanding chronic disease, which requires emotional adaptation [1]. Previous research has shown that alexithymia is a risk factor for depression [15], which is deleterious for patients with diabetes [4–7]. Also, a deficit in the awareness of affects results in abnormal physiological reactions and impaired capacity for self-care [13]. An advanced capacity for self-care is necessary in diabetes.

For this reason, we were interested in finding interventions focusing on increased emotional awareness and verbal expressiveness. We have chosen to test the ASSA [30, 32, 37] against BBAT [34–36] in two studies. In Study I, we perform a two-arm randomized controlled trial with patients with type 1 or type 2 diabetes from one hospital diabetes outpatient clinic. In Study II, ASSA, BBAT and ‘treatment as usual’ will be compared in a three-arm randomized controlled trial for patients with type 2 diabetes from primary care units.

We expect the ASSA method to be more efficient than BBAT in reducing depressive symptoms. In the ASSA intervention, patients are systematically trained to identify and describe feelings, and are also presented with advanced affect theory. In BBAT, patients focus more on bodily features, such as breathing, grounding, stability, centring, flexibility and flow [36]. The patients undergoing BBAT are not systematically trained to identify and describe feelings but they are encouraged to observe and accept sensations and emotions that awaken during the treatment sessions [36]. As neither of the two interventions is ‘placebo’, we think it is important to compare both ASSA and BBAT with treatment as usual.

We have chosen reduction of depression symptoms as the primary outcome measure, even though some patients were not depressed at the time of inclusion. A reduction in depression symptoms might be of value even for patients not fulfilling our criteria for self-reported depression. A lower cut-off level (≥5 points) has been proposed for the depression subscale of the Swedish version of Hospital Anxiety and Depression Scale than we have chosen to use. This means that the sensitivity for depression might be less than optimal in our study [39].

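### Study II's aim is a set of contrasts with usual care, but its only named primary between-arm test, and its sample size, rest on an omnibus three-group test

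*Protocol article*

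**What the plan says.** - **Aim** (Objective and research questions, Study II): "The main aim is to compare ASSA, BBAT with only treatment as usual". The Discussion repeats the wish to set both therapies against usual care, because neither is regarded as inert, and adds an expectation: "We expect the ASSA method to be more efficient than BBAT in reducing depressive symptoms".
- **Primary outcome** (Primary and secondary outcome measures): "In both studies, the primary outcome measure is the change in depression symptoms".
- **Test** (Statistical analysis, Study II): "The Kruskal–Wallis test will be used for changes in non-normally distributed variables (psychological symptoms and midnight salivary cortisol concentration"). The joint section for Studies I and II adds a paired t test for HbA1c and regressions of outcomes on baseline characteristics. Neither is presented as a comparison of arms on depression.
- **Sample size** (Power calculations for sample size, Study II): the calculation assumes a pattern "where two groups have the same means and one differs with 1.4 points". Study I's SD of 2.8 is carried over. One-way ANOVA at 80% power gives 60 per arm, and 15% is then added for the Kruskal–Wallis test, giving 70.

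**The concern.** The aim asks how each therapy compares with usual care, and those are pairwise questions. The Kruskal–Wallis test asks whether all three arms are alike. If it is significant, the reader learns only that they are not. That would be so if ASSA alone beat usual care, if both therapies did, or if one therapy did worse. Followed as written, the stated test does not answer the stated aim.

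The sample size has the same problem. The 80% is the chance that the omnibus test rejects when two arms are identical. It is not the chance of showing that a given therapy differs from usual care. A reader who takes 70 per arm as 80% power for the aim reads more into it than was calculated.

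**Working it through.** **Inputs.** From the Study II power section: difference 1.4 points, SD 2.8, power 80%, 15% allowance, 70 per arm. From Statistical analysis: alpha 0.05. Equal allocation is assumed from the equal arm sizes.

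**1. The plan's own figure.** One-way ANOVA, noncentral F with 2 and 3n − 3 degrees of freedom, λ = n × Σ(mᵢ − m̄)² / SD².
- Means 0, 0, 1.4: m̄ = 0.467, Σ = 0.218 + 0.218 + 0.871 = 1.307, and 1.307 / 7.84 = 0.1667.
- n = 60: λ = 10.0, power 80.8%. n = 59 gives 80.1%.
- 60 × 1.15 = 69, stated as 70.

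The figure reproduces.

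**2. Power for a single 1.4-point contrast at 70 per arm.** Two-sided t test, noncentrality 1.4 / (2.8 × √(2/70)) = 2.96.

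| Alpha per contrast | t test | with 15% allowance (normal approximation) |
|---|---|---|
| 0.05 | 83.6% | 78.8% |
| 0.025 (two contrasts with usual care) | 75.5% | 69.7% |
| 0.0167 (all three pairs) | 70.3% | 64.2% |

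**3. The same contrast behind an omnibus gate.** Simulation with normal data, SD 2.8 and 70 per arm: Kruskal–Wallis at 0.05, then pairwise rank tests at 0.05 only if it is significant. With two arms equal and the third 1.4 points away, each true 1.4-point contrast is declared in about 77–78% of trials. The omnibus test itself rejects in about 85%.

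**4. Why the gate suffices with three arms.** If any two of the three pairwise null hypotheses are true together, all three arms are equal, and the omnibus test covers that case at 0.05. If exactly one is true, only one false rejection is possible, and it is tested at 0.05. Family-wise error is therefore at most 5% with no further correction.

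**5. Sensitivity of the omnibus power (assumption, not in the article).** The article gives no spacing for the three means. Suppose the total spread is 1.4. With the middle arm at 0.7, Σ = 0.49 + 0.49 = 0.98 and 0.98 / 7.84 = 0.125. At 70 per arm:

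| Middle arm | 15% allowance (n/1.15 = 60.9) | Relative efficiency 0.955 (n × 0.955 = 66.9) |
|---|---|---|
| Equal to one of the others | λ = 10.14, 81.5% | λ = 11.14, 85.2% |
| 0.35 from one end | 72.5% | 76.7% |
| Midway (0.7) | λ = 7.61, 68.8% | λ = 8.36, 73.1% |

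Direct simulation of the Kruskal–Wallis test with normal data gives 85% and 73% for the first and last rows. In the midway case, under the gated procedure, the 1.4-point contrast is declared in about 72% of trials and each 0.7-point contrast in about 29%. A wider spread raises omnibus power: means 0, 0.7, 2.1 give 97% with the allowance.

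**The case against.** **The follow-up tests may be in a plan that is not shown.** This is a journal article, and pairwise tests after an omnibus test are often left to the analysis plan. That stands as far as it goes: their absence is not in itself the error, and nothing in the article says that ungated pairwise tests are intended. What remains is what the article does fix. It names an omnibus test for the primary outcome and derives its sample size from that test, while stating an aim made of contrasts. A later plan can add contrasts, but it cannot make the published 80% refer to them.

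**The 80% might be thought to overstate power under the team's own expectation.** A reader might infer this because the Discussion expects ASSA to do better than BBAT and treats both as active, which suggests three different means and a figure near 69%. The article does not support that inference. It gives an order but no sizes. The 69% needs a total spread of exactly 1.4 points, BBAT exactly midway, and the 15% allowance. For a 1.4-point spread that is the least favourable pattern. The opposite reading is equally open. Study I, which compares ASSA with BBAT, is sized on 1.4 points. If ASSA exceeds BBAT by 1.4 and BBAT is no worse than usual care, the means are 0, d, d + 1.4, and power with the allowance is 81.5% at d = 0, 91% at d = 0.35 and 97% at d = 0.7.

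**The assumed pattern can fit the aim.** The power section does not say which arm differs. Two equally effective therapies against usual care would match the aim and has the same power. This is right, although it sits awkwardly with the expectation that ASSA is better.

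**Conclusion.** The point holds as a mismatch between the aim and the test and sizing given for it. A significant Kruskal–Wallis result does not identify the arm, the direction or the size of a difference, and the stated 80% belongs to the omnibus test with two identical arms. The sample-size arithmetic is not wrong.

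The size is moderate. Under the gated procedure a 1.4-point contrast at 70 per arm has about 77–78% power, assuming normal data, SD 2.8 and two equal arms. Splitting alpha instead lowers it to 70–76% (two contrasts) or 64–70% (three).

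The article does not establish that the omnibus power is overstated. On the assumption of a 1.4-point total spread it runs from about 69% to 81% with the 15% allowance, or about 73% to 85% for Kruskal–Wallis with normal data, and it is higher if the spread is wider. That range belongs in the plan as a labelled assumption.

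**What to change.** - Name the three contrasts on the primary outcome: ASSA–usual care, BBAT–usual care and ASSA–BBAT.
- Run the Kruskal–Wallis test at 0.05. Only if it is significant, test each pair at 0.05. State that with exactly three arms this is a closed procedure, so family-wise error stays at 5%.
- Report each difference in points on the depression subscale of the Hospital Anxiety and Depression Scale, with a 95% confidence interval, whether or not the test is significant.
- In the power section, say that the 80% refers to the omnibus test with two equal arms. Add that a 1.4-point contrast has about 77–78% power at 70 per arm under the procedure above when two arms are equal. Give the omnibus range for a middle arm (about 69–81% with the 15% allowance, 73–85% with normal data, for a 1.4-point spread) as an assumption.

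The cost is analysis wording and a slightly less favourable stated power. No extra patients are needed. The article describes Study II recruitment as still to start, so the change can precede any Study II data.
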